# Yoga versus health education for persistent fatigue in patients with post-COVID-19 syndrome: protocol for a multicentre randomised controlled trial

**DOI:** 10.1136/bmjopen-2025-107840

**Published:** 2025-10-23

**Keywords:** post-acute COVID-19 syndrome, fatigue, clinical protocols

## Abstract

**Introduction:**

Post-COVID-19 syndrome, defined by persistent symptoms lasting beyond 12 weeks of a SARS-CoV-2 infection, affects both severe and mild COVID-19 cases. Fatigue is the most common symptom, impacting 58% of patients. Other symptoms include mental symptoms, cardiovascular and respiratory issues and autonomic dysfunction. Chronic inflammation and immune dysregulation seem to be associated with post-COVID-19 fatigue. Despite its impact on healthcare and the economy, effective treatments are limited. Yoga and health education have been shown to be effective for fatigue in other related conditions. The aim of this study, therefore, is to investigate the efficacy, safety and cost-effectiveness of yoga and health education on post-COVID-19 persistent fatigue.

**Methods and analysis:**

A randomised controlled trial with 100 patients with persistent fatigue due to post-COVID-19 syndrome is being conducted at three study centres. Patients are randomised to two interventions, yoga and health education. Both interventions include 12 weeks of 90 min supervised group sessions and 60 min of home practice per week. The primary outcome measure is fatigue on the Chalder Fatigue Scale 12 weeks after randomisation. Secondary outcome measures include postexertional malaise (DePaul Symptom Questionnaire), health-related quality of life (Short Form Health Survey-12 Item Version, EuroQol 5-Dimension 5-Level Questionnaire), anxiety, depression (Hospital Anxiety and Depression Scale), stress (Perceived Stress Scale), sleep quality (Pittsburgh Sleep Quality Index), hand grip strength, laboratory parameters and adverse events. Physical activity analysis over 7 days using a body-worn sensor and 24-hour heart rate variability using a 3-channel ECG recorder are assessed exploratively. All outcome measures will be assessed 12 and 24 weeks after randomisation. In addition, health economic analyses as well as mediator and moderator analyses including self-reported body awareness, self-efficacy, personality traits and treatment credibility/expectations will be conducted. Furthermore, qualitative interviews at week 12 will be carried out.

**Ethics and dissemination:**

The trial received ethical approval from the Ethics Committee of the University Hospital Tübingen (approval number: 775/2022BO2). Results will be disseminated via peer-reviewed open-access publications, scientific conferences and targeted communication to patient organisations, healthcare providers and the wider public.

**Trial registration number:**

NCT05890599.

STRENGTHS AND LIMITATIONS OF THIS STUDYThis multicentre randomised controlled trial includes an active control group (health education), allowing for a more rigorous evaluation of yoga-specific effects beyond non-specific attention and group interaction.The study uses a comprehensive set of both subjective (eg, fatigue, quality of life) and objective (eg, hand grip strength, heart rate variability, activity sensors) outcome measures.The inclusion of health economic evaluation from a societal perspective provides valuable insights into the cost-effectiveness of interventions.The qualitative component enables in-depth exploration of participants’ subjective experiences, complementing the quantitative findings.Due to the nature of behavioural interventions, blinding of participants is not feasible, which may introduce expectancy or reporting bias.

## Background

 Patient data from around the world show that the health of patients suffering from COVID-19 can be impaired by late effects months after acute infection.^1^,^5^ The National Institute for Health and Care Excellence (NICE) guideline and the German guideline on long covid/post-COVID-19 characterise post-COVID-19 syndrome as a symptom cluster that occurs within 12 weeks of SARS-CoV-2 infection, lasts for at least 8 weeks and cannot be explained by another diagnosis.^6 7^ Symptoms can persist after an acute COVID-19-19 infection or reappear after initial recovery.^6 8^

The prevalence of post-COVID-19 syndrome among patients with a severe course of the disease and a resulting hospitalisation is reported to be up to 80%.^9^ However, patients with supposedly mild courses can also be affected.^9 10^ Fatigue is the most frequent and disabling symptom, reported by around one-third of patients overall and by 58% of those with post-COVID-19 syndrome.^9^

In addition to fatigue, respiratory and cardiovascular complaints are common. Organ damage has mainly been described in patients with ‘postintensive care syndrome’.^11^,^13^ Cardiovascular manifestations include tachycardia, palpitations and postural orthostatic tachycardia syndrome.^9 14 15^ Alterations in cardiac autonomic function, particularly reduced heart rate variability (HRV), have been reported.^16^,^18^ Such dysautonomia is also known from cancer-related and other postviral fatigue syndromes.^18 19^

Fatigue is a severe exhaustion on a somatic, functional, cognitive and/or psychological level that is disproportionate to the previous exertion and does not improve sufficiently with rest.^20^ It has been observed after various viral infections and partly overlaps with myalgic encephalomyelitis/chronic fatigue syndrome (ME/CFS).^20^,^22^ Proposed mechanisms include low-grade inflammation, autoimmunity, virus persistence, autonomic dysfunction and microthrombi.^23^,^27^ Postexertional malaise (PEM), an acute exacerbation of symptoms after exertion, is also frequently reported.^728^,^30^

Post-COVID-19 fatigue has substantial consequences for quality of life, social participation and work capacity, with high socioeconomic costs.^31^,^34^

The treatment of fatigue has so far mainly been investigated in the context of cancer-related fatigue.^35^ Among non-pharmacological approaches, physical activity is considered most effective.^35^,^38^ However, for patients with post-COVID-19, exercise tolerance is often limited, and standard programmes may trigger PEM.^7 39^ The Association of the Scientific Medical Societies in Germany (German: Arbeitsgemeinschaft der Wissenschaftlichen Medizinischen Fachgesellschaften, AWMF) S1-long covid/post-COVID-19 guideline recommends exercise therapy with a biopsychosocial focus and the core components of endurance and strength training supervised by trained personnel as part of rehabilitation in patients with post-COVID-19 syndrome.^7^ One lower-intensity form of physical activity could be yoga.

Yoga combines physical postures, breathing techniques and meditative elements.^40^ In recent decades, it has been increasingly applied as a therapeutic intervention. Objectives include strengthening the body, enhancing body awareness and promoting stress regulation and self-efficacy.^40^ Practices can be adapted to individual functional levels, enabling fatigue-paced group sessions.

Yoga research in clinical populations—including cancer, depression, cardiac arrhythmias, chronic back pain and type 2 diabetes—demonstrates preventive and therapeutic benefits, reducing stress, anxiety, depression, sleep disorders, pain and fatigue, while improving quality of life, mood, sleep and inflammatory processes.^35^,^3741^

Furthermore, beneficial effects on cardiovascular regulation and HRV have been reported.^55 56^ Yoga is generally safe and associated with good adherence.^57^

Taken together, yoga may address both the physical and psychological symptom clusters of post-COVID-19 syndrome and thus represent a promising therapeutic approach.^58 59^

### Objectives

The aim of this study is to investigate whether yoga is a useful therapeutic approach for post-COVID-19 persistent fatigue. The primary objective of this intervention study is to evaluate the short-term effect of yoga in addition to routine care on fatigue in patients with post-COVID-19 compared with health education in addition to routine care. Secondary objectives include the evaluation of medium-term effect on fatigue as well as short-term and medium-term effect of a yoga intervention in addition to routine care on health-related quality of life, mental health symptoms, performance limitations, sleep quality, stress and inflammation in patients with post-COVID-19 syndrome compared with health education in addition to routine care. The safety of the interventions is being investigated through close monitoring of adverse events (AEs). The study further uses cost-effectiveness and cost-utility analysis to investigate how cost-effective the yoga group is compared with the health education group. Furthermore, qualitative interviews will be conducted following the interventions to capture the subjective experiences of the patients.

## Methods

### Study design

The study is designed as a multicentre, single-blind randomised controlled trial with two study arms. The outcome assessor is blinded to group allocation. The study protocol is reported according to the Standard Protocol Items: Recommendations for Interventional Trials guideline.^60^

The study centres are the Institute of General Practice & Interprofessional Care at the University Hospital Tübingen, the Robert Bosch Center for Integrative Medicine and Health at Bosch Health Campus Stuttgart and the Charité Integrative Medicine Outpatient Department at Immanuel Hospital Berlin-Wannsee. A period of 12 weeks after randomisation is scheduled per participant until the primary outcome measure is collected (figure 1). Sustainability will be assessed as a follow-up after 6 months.

**Figure 1 F1:**
[figure not shown]
SPIRIT-recommended content for the schedule of enrolment, interventions and assessments. HRV, heart rate variability; SPIRIT, Standard Protocol Items: Recommendations for Interventional Trials.

###  Ethical approval, trial registration and trial status

The research ethics committee of the University Hospital Tübingen (approval number: 775/2022BO2) granted ethical approval prior to participant recruitment. The trial was initially registered with ClinicalTrials.gov (NCT05890599) on 2 June 2023, based on protocol V.1.0, prior to participant recruitment. A first amendment dated 6 June 2023 added the following to the measurements: the questionnaires EuroQol 5-Dimension 5-Level Questionnaire (EQ-5D-5L), Short Form Health Survey-12 Item Version (SF-12), PEM-DePaul Symptom Questionnaire (DSQ), Body Awareness Questionnaire (BAQ) and Big Five Inventory (BFI-­10); the laboratory parameters D-dimers, lactate dehydrogenase (LDH), leucocytes and lymphocytes as well as assessments of hand grip strength (HGS), real-world physical activity and HRV. A second amendment dated 14 June 2025 added the qualitative aspects to the study. All amendments and updated protocol versions were communicated to ClinicalTrials.gov to ensure transparency. This manuscript refers to V.1.3 of the protocol (17 January 2025), which incorporates these updates. Participant recruitment started in 10 June 2023 and is planned to be completed by September 2025. The study is expected to be completed by March 2026.

### Study population 

Patients with persistent fatigue as a result of post-COVID-19 syndrome are included in the study population. Based on the German long covid/post-COVID-19 S1 guideline (as of 5 March 2023), three categories are used to diagnose post-COVID-19 syndrome: (1) symptoms that persist after the acute COVID-19 infection or its treatment, (2) new symptoms that occur after the end of the acute phase but can be understood as a consequence of SARS-CoV-2 infection and (3) worsening of a pre-existing condition as a result of SARS-CoV-2 infection.^7^

The definition given in the widely used NICE guidelines states that post-COVID-19 syndrome includes ‘signs and symptoms that develop during or after an infection consistent with COVID-19, continue for >12 weeks and are not explained by an alternative diagnosis. It usually presents with clusters of symptoms, often overlapping, which can fluctuate and change over time and can affect any system in the body’.^6^ To differentiate from patients with long covid syndrome, patients are only included if symptoms persist for > 12 weeks.

### Inclusion and exclusion criteria

#### Inclusion criteria

Confirmed COVID-19 infection, diagnosed by PCR or serology (SARS-CoV-2 IgG/IgA).Subsequent symptoms (as described in the NICE guidelines) lasting >12 weeksSelf-assessment that the fatigue is a consequence of COVID-19 disease.Presence of persistent fatigue, operationalised by scores ≥4 on the binomial Chalder Fatigue Scale (CFQ).^61^Age 18–65 years.

#### Exclusion criteria

Chronic disease or regular use of medication that is associated with fatigue (eg, untreated hypothyroidism, diabetes, autoimmune diseases, anaemia defined as haematocrit <24, chronic fatigue syndrome due to causes other than COVID-19, endocrinopathies, cancer, heart failure).Indications that fatigue is primarily caused by another medical or psychiatric condition other than post-COVID-19 (eg, major depression, insomnia, sleep apnoea).Indications that fatigue is primarily caused by other factors (eg, shift work, recent change in activity or schedule).Physical limitations or conditions that preclude participation in the yoga intervention (eg, severe neck injuries, unstable joints, severe pre-existing cardiovascular disease, organ failure (kidney, liver, etc), acute febrile infection, severe neurological diseases).Pregnancy or breastfeeding.Simultaneous participation in other clinical trials.Simultaneous participation in other yoga interventions.

### Recruitment 

Participant recruitment takes place via notices and leaflets at the University Hospital Tübingen, the Bosch Health Campus Stuttgart, Charité - Universitätsmedizin Berlin and in post-COVID-19 focused practices and self-help groups in the regions, as well as via calls in the local media and in social networks (eg, Instagram). Potential participants are screened by telephone. If the eligibility criteria are preliminarily met, the inclusion and exclusion criteria will be checked by an experienced researcher at the respective study centre and an anamnesis and physical examination will be carried out by an experienced study physician to further assess eligibility as well as the feasibility and safety of the study interventions and measurements for the specific participant. If the inclusion criteria are met, there are no exclusion criteria, and the interventions and measurements are deemed feasible and safe, participants can be included in the study. All prospective participants first receive detailed verbal and written information on the study and have the opportunity to ask questions. A written informed consent declaration is required before participation in the study.

### Randomisation 

After completion of the measurements at week 0, eligible participants will be assigned to one of two study arms, the yoga group or the health education group, via block randomisation (stratified by gender and study centre) with randomly varying block length. The randomisation sequence was created by an external scientist who has no participant contact during the entire study using R software (V.4.3.1). The randomisation list will be kept password-protected and only the scientist creating the list has access to it. Allocation concealment is ensured by central randomisation via Research Electronic Data Capture (REDCap) software. Once a participant has been randomised by the study physician, their data can no longer be changed in REDCap. Neither the participants nor the study physicians nor the study coordinators have insight into the randomisation sequence.

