### Sample size calculation

The study is powered to detect a minimal clinically relevant effect of 3.3 points on the CFQ.^61^ Based on an SD of 4.4 in a sample of patients with post-COVID-19 syndrome and fatigue diagnosed by CFQ,^62^ the estimated effect size is d=0.75. Assuming this effect, a two-tailed independent t-test with a significance level of α=0.05 requires a total of 78 participants to detect a group difference with a power of 90%. In order to avoid a possible loss of power due to a dropout rate of up to 20%,^63^ it is planned to include 100 participants in the study and assign them to the two study groups in a 1:1 ratio. Sample size calculation was performed using the ‘pwr’ package in R V.4.3.1.^64^

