### Statistical analysis

All analyses are based on the intention-to-treat population, that is, all participants included in the study are analysed in the group to which they were originally assigned, regardless of the treatment they actually received. Missing values are handled using multiple imputation. The multiple imputation procedure will be conducted using R (V.4.3.1), employing the ‘missForest’ package for handling missing data.^91^ The multiple imputation procedure using the ‘missForest’ package involves handling missing values by employing a non-parametric approach. This package uses a Random Forest algorithm to predict missing values based on the observed data, accommodating both numerical and categorical variables. Through iterative variable iterations, missing values are imputed by leveraging predictions from the remaining variables within the dataset. In addition, a per-protocol analysis is conducted as a sensitivity analysis. The per-protocol population is defined as all participants who provide data at the respective time point and participate in at least 8 of the 12 intervention appointments.

The primary outcome measure is analysed confirmatory using a univariate analysis of covariance, in which the primary outcome measure is modelled as a function of group allocation (fixed factor), study centre (binary covariate), treatment credibility and expectation (linear covariates) and the respective baseline values (linear covariate). Within this model, the adjusted group difference and its 95% CI are estimated and tested for superiority of the intervention over the control group using a two-sided t-test at the α=0.05 level. The secondary end points are analysed exploratively (without correction for multiple testing) using the same models as the primary end point. To estimate the clinical significance of the results, change scores and effect sizes (Hedges’ g) are calculated for between-group comparisons.

HRV parameters within groups will be compared at two different time points using a Wilcoxon signed rank test. The results will be presented as medians and IQRs, Hodges-Lehmann estimator (HLE) of the differences, 95% CI and effect sizes r. A comparison between groups will be undertaken by examining the HLE, the 95% CI and the effect sizes r simultaneously.

All analyses will be conducted using R V.4.3.1, with the ‘psych’‘ package used for psychometric assessments.^92^

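### Gender stratifies the randomisation but is left out of the confirmatory ANCOVA; the analysis stays valid but is mildly conservative if gender predicts the outcome

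*Protocol article*

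**What the plan says.** Under Randomisation, the protocol article allocates participants "via block randomisation (stratified by gender and study centre) with randomly varying block length". Gender and study centre are therefore both design factors.

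Under Statistical analysis it states: "The primary outcome measure is analysed confirmatory using a univariate analysis of covariance". The outcome is "modelled as a function of group allocation (fixed factor), study centre (binary covariate), treatment credibility and expectation (linear covariates) and the respective baseline values", and the adjusted group difference is "tested for superiority of the intervention over the control group using a two-sided t-test at the α=0.05 level". Each term is named with its type (fixed, binary or linear). Centre is carried over from the randomisation and gender is not. The same section applies these models to the secondary endpoints, as exploratory analyses without multiplicity correction.

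Under Sample size calculation, the trial is "powered to detect a minimal clinically relevant effect of 3.3 points on the CFQ", with the SD taken as follows: "Based on an SD of 4.4 in a sample of patients with post-COVID-19 syndrome and fatigue diagnosed by CFQ". The calculation is a two-tailed independent t-test and includes no covariates.

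**The concern.** Blocking within gender makes the arms nearly equal in gender mix. Differences between genders then contribute almost nothing to the true sampling variance of the treatment contrast. A model without gender still leaves that variation in its residual, so the standard error it reports is larger than the true one. The design secures the balance and the analysis does not use it.

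At stake are the width of the confidence interval and a little power on the one confirmatory test. The omission carries over to the secondary endpoints. Hand grip strength in kilograms is the one where a gender difference is easiest to imagine, although its baseline value is also in the model and may absorb most of that difference.

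**Working it through.** **1. The plan's own figure.** Inputs from Sample size calculation: difference 3.3, SD 4.4, so d = 3.3/4.4 = 0.75; two-sided α = 0.05; power 90%. The exact noncentral-t solution is 38.35 per arm, rounded up to 39, total 78. This reproduces the stated 78. For 20% dropout, 78/0.80 = 97.5, so 98 are needed and 100 are planned. With 100 randomised and 20% lost, 80 are analysed.

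**2. Assumption.** Let R² be the share of outcome variance remaining after the other covariates that gender explains. The documents give no value, so 0%, 2%, 5% and 10% are tried.

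**3. Closed form (perfect gender balance, normal test).**
- Ratio of reported to true SE = 1/√(1 − R²): 1/√0.98 = 1.010; 1/√0.95 = 1.026; 1/√0.90 = 1.054.
- Actual type I error = 2[1 − Φ(1.96/√(1 − R²))]: 4.8%, 4.4% and 3.9%.

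**4. Simulation without those idealisations.** 80 analysed; gender by three-centre strata; random blocks of 2 or 4; 70% in one gender; residual SD 4.4; least squares with centre as three levels, fitted with and without gender to the same data sets. There were 20,000 null replicates and 10,000 with a true difference of 3.3. The gender split and block sizes are assumptions. Baseline, credibility and expectation were not simulated; 4.4 stands for the SD that remains.

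| R² | Type I error, without / with gender | Mean SE (null runs), without / with | Power, without / with |
|---|---|---|---|
| 0% | 4.93% / 4.92% | 0.981 / 0.982 | 91.44% / 91.29% |
| 2% | 4.62% / 4.84% | 0.982 / 0.973 | 91.22% / 91.54% |
| 5% | 4.32% / 4.90% | 0.982 / 0.957 | 91.28% / 92.04% |
| 10% | 3.96% / 4.87% | 0.983 / 0.932 | 91.68% / 93.21% |

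The Monte Carlo standard error of a type I figure is √(0.05 × 0.95/20,000) ≈ 0.15 percentage points. The power gain from adding gender is 0.32, 0.76 and 1.53 points at 2%, 5% and 10%. At 0% the extra term costs 0.15 points. The two methods agree in direction and closely in size.

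**5. Scale of the assumption.** With a 70:30 split, the gender difference implied by R² is 4.4 × √(R²/(0.7 × 0.3)): 1.4 points at 2%, 2.1 at 5% and 3.0 at 10%. The top of the range therefore needs an adjusted gender gap almost as large as the 3.3-point target effect.

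**The case against.** The strongest reply is that the documents show no loss at all. Precision suffers only if gender predicts 12-week fatigue beyond baseline fatigue, centre, credibility and expectation, and nothing in the article says that it does. Even if it does, the error is in the safe direction and small, on power already above 91% with 80 analysed. The secondary analyses are exploratory, so a slightly conservative p-value there has no confirmatory consequence. All of this stands, and it limits the size of the point.

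It does not remove the mismatch. This is not a detail left to an unseen analysis plan, because the article itself lists the model's terms and includes one stratification factor but not the other.

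A reader might infer that the omission biases the estimate, inflates false positives, makes the sample too small, or certainly wastes precision. The documents support none of these. Randomisation keeps the estimate unbiased. The type I error falls rather than rises. The 78 comes from a test with no covariates. Any loss is conditional on an association that the documents do not quantify.

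The same sentence also calls centre a binary covariate although the trial "is being conducted at three study centres". That inconsistency needs no assumed R² and is in that sense firmer, but it is a separate matter and does not answer this one.

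**Conclusion.** The mismatch between design and analysis is certain; its numerical consequence is conditional. If gender explains 2% to 10% of the residual variance, the reported SE is about 1% to 5% too large, the nominal 5% test runs at about 4.6% to 4.0%, and power is about 0.3 to 1.5 percentage points below what the same data would give with gender included. If gender explains nothing, nothing is lost. These figures assume 80 analysed, residual SD 4.4, a 70:30 gender split and small blocks. For grip strength and the other secondary endpoints, the documents give no basis for a number. This is an inexpensive correction worth making, and it does not threaten the trial's validity.

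**What to change.** Add gender as a categorical fixed factor to the primary ANCOVA and to the models that copy it, or state why it is omitted. Record the change with a date before outcome data are analysed, so that it cannot look data-driven; the article expects completion by March 2026. The cost is one degree of freedom if gender has two categories, and no new data, since gender is already recorded to randomise. If gender turns out to be unrelated to the outcome, the simulated price is about 0.15 percentage points of power. The sample size need not change. The same edit can correct the description of centre to a three-level factor, so that both stratification factors enter the model as they were used in the randomisation.
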